### Criteria for discontinuing or modifying allocated interventions {11b}

There are no known specific risks or side effects of SEE. However, putative side effects of the intervention (e.g., worsening of symptoms, hospitalization, or suicidality) are monitored. An independent data monitoring and safety committee (IDMC) is employed. Participants are able to discontinue the trial at any time without having to give further explanation. Discontinuation has to be documented for the individual participant.

### Strategies to improve adherence to interventions {11c}

The fidelity of SEE is being assessed every 3 months throughout the trial by the IPS Fidelity Scale for Young Adults. This is a 35-item scale developed by the IPS Employment Center [30] and presents a diversification of the IPS-25 fidelity scale [31] specifically tailored to the young adult population. It has two components that are scored separately: the IPS-EMP(loyment) part comprises 25 employment items while the IPS-ED(ucation) part comprises nine education items and one family contact item. Sum Scores range from 0 to 125 for the EMP-part and from 0 to 50 for the Ed-part of the Fidelity Scale. The implementation fidelity refers to the degree to which an intervention is delivered as intended. An IPS-EMP score of 100 or higher indicates good fidelity in IPS employment while an IPS-ED score of 40 or higher indicates good fidelity in IPS education [18, 30].

### Relevant concomitant care permitted or prohibited during the trial {11d}

All participants will receive TAU for adolescents and young adults with early psychosis in an outpatient psychiatric setting for the duration of the trial. Participants of the control group cannot receive SEE for the duration of the trial.

### Provisions for post-trial care {30}

All participants will continue TAU post-trial care. Additionally, participants of the control group will be offered SEE post trial, if available at the respective mental health service.

## Outcomes {12}

### Primary outcome

In reference to international studies [9, 22, 32–34], the primary outcome of SEEearly is the binary indicator “participating steadily over at least 50% of the 12-month follow-up in competitive employment and/or mainstream education,” which includes the dimension of sustained involvement. A similar outcome “participating steadily over at least 50% of the 12-month follow-up in competitive employment” has been frequently proposed as a valid primary outcome to operationalize sustainability of IPS interventions and has been used successfully as primary outcome in IPS RCTs in people with severe mental illness [32, 35].

The primary endpoint was chosen as mainstream education aims to a formal qualification or degree, which includes an extended period of time. The primary outcome will be assessed monthly.

### Secondary outcome

As secondary outcomes, in accordance with relevant studies in the area [36, 37], we monthly assess “*time to first competitive job and/or mainstream education*” (measured in days), “*length of competitive employment and/or mainstream education*” (measured in days), comprising part- and full-time positions, as well as seasonal or temporary positions depending upon the business needs of an employer [18], “*monthly wages*” (measured in Euro) and “*educational attainment*” (measured in degrees/qualifications and ECTS [European Credit Transfer System] points per semester). Furthermore (see also Table 1), secondary non-vocational outcomes are measured at baseline and 6- and 12-month follow-up. It includes psychopathology, functional impairment, substance use, subjective quality of life, and motivation for change. Ongoing psychiatric treatment and ongoing medication as secondary non-employment outcomes are measured monthly.

## Participant timeline {13}

The participant timeline is shown in Fig. 1.

## Sample size {14}

The sample size calculation was based on the primary dichotomous outcome “*steady participation for at least 50% of the 12-month follow-up period in competitive employment and/or mainstream education*” as used in prior studies [22, 32, 38]. Here, the reported steady participation in competitive employment rates vary between 44 and 39% for IPS vs. 11 and 23% for TAU. To detect differences of 24% between the two groups and 40% in the IPS arm vs. 16% in the control arm, the required sample size to find a significant effect with a power of 0.9 at a two-sided significance level of 0.05 is given by 144 participants (72 per arm). The sample size calculation is based on a *χ*^2^-test. As the logistic regression model adjusted for the study site which is used for the primary efficacy analysis yields a power increase compared to the *χ*^2^ test (i.e., the latter ignores the influence of study site effects), this strategy for sample size calculation defines a conservative procedure. The power calculation was performed using NQuery Version 8.4.1.0. Published drop-out and lost to follow-up rates in SE and SEE trials range from 5% [39] to 30% [27]. In a pilot RCT at the study center Berlin I, the drop-out rate was 22%. Assuming a drop-out rate of 22%, the total number of participants to be recruited is thus 184.

## Recruitment {15}

Recruitment is taking place in the outpatient units of the involved sites. Clinicians and/or psychologists refer patients interested in participating in the study to a research assistant who, in turn, schedules an appointment. To secure continuous recruitment of participants, the SEEearly project leader of the sites and the research assistants are in continuous exchange with the clinical staff to provide a constant reminder of the study. Furthermore, study information is available via posters, leaflets in waiting rooms and clinical units and a website.

## Assignment of interventions: allocation

### Sequence generation {16a}

After signing informed consent and immediately after baseline assessment the randomization is carried out, using a computer-generated randomization list that is integrated in the electronic data capture system (EDC). Participants are randomly assigned to one of the two arms with a 1:1 ratio.

### Concealment mechanism {16b}

N/A. Participants are assigned by the SEE-specialists to either intervention or control group immediately after randomization takes place.

### Implementation {16c}

A research assistant (psychologist) assesses the patients for eligibility and provide written and verbal information about the research project and answers existing questions. Before signing the informed consent, underage participants need the consent of a parent or guardian (Participant Information Sheet for Adults, Adolescents, Custodian and Participant Consent Form in German are available from the corresponding author on request). The SEE-specialists perform the randomization and treatment allocation. The latter also inform the participant about the results of the randomization. Participants assigned to the intervention group start the SEEearly treatment at the latest 1 week after allocation. Participants assigned to the control group continue TAU in the outpatient unit.

## Assignment of interventions: blinding

### Who will be blinded {17a}

It is not feasible nor possible for the participating patients and most project staff to be blinded to treatment allocation. However, the research assistants assessing the primary outcome are blind to the intervention group. Participants are instructed not to disclose details of their treatment to the research assistants.

### Procedure for unblinding if needed {17b}

N/A. Research assistants assessing primary and secondary outcomes will not be unblinded during the trial. If unblinding occurs (e.g., the participant reveals allocated intervention to the research assistant), this will be documented in the participant’s file.

## Data collection and management

### Plans for assessment and collection of outcomes {18a}

Comprehensive baseline assessment and 6 and 12 months of follow-up assessments are done face-to-face or, if not possible, via video-calls by a research assistant. Each research assistant has completed a specific training prior to the start of the trial. Monthly assessment of the primary outcome, current medication, and psychiatric treatment is done face-to-face, via video-calls, or telephone. Loss of masking of treatment allocation is being documented. The reliability and validity of assessments will be examined. The baseline assessment includes diagnoses according to ICD-10 (International Statistical Classification of Diseases and Related Health Problems, version 10) and DSM-5, sociodemographic information, including education/employment and housing situation, psychiatric treatment prior to the trial, and motivation for change regarding employment/education. Furthermore, we will use the following validated questionnaires to assess mental health status, substance use, and quality of life at baseline and the follow-ups:*Psychopathology* will be measured with the well-established observer-rated Positive and Negative Syndrome Scale (PANSS; [40]). This scale is widely used and known as the “gold standard” for psychopathological outcomes of interventions in people with psychotic disorders [41].*Functional impairment* with regard to occupational activity and participation will be assessed due to its tight connection to the aim of SEE. This will be realized by observer ratings on the short version of the International Classification of Functioning, Disability, and Health (Mini-ICF-APP) instrument. This widely applied instrument is used to quantify disability [42] and allows for comparing results of the presented trial with other RCTs [43]. As a global assessment to measure functionality and to ensure comparability with other studies, we also use the Global Assessment of Functioning (GAF; [44]).*Substance use* history and past month substance use will be measured by a modified version of the Addiction Severity Index (ASI; [45–47]. Since the comorbidity of *cannabis use* and psychosis has been widely discussed, a German version of the Daily Sessions, Frequency, Age of Onset and Quantity of Cannabis Use Inventory (DFAQ-CU) will be used to specifically assess abuse of cannabis with a focus on frequency, age of onset, and quantity of consumption [48].*Subjective quality of life* will be measured with the WHOQOL-BREF [49], a short version of the WHOQOL-100 (World Health Organization Quality of Life scale). This self-rating instrument presents with high rates of internal consistency (*α* = 0.57 to *α* = 0.88) and is translated into 30 languages, which allows for comparison with international research results.Economic outcomes will be assessed in terms of *social return on investment* (SROI) at last follow-up after 12 months. This measure is designed to survey the value of social benefits created by a program in relation to the relative cost of achieving those benefits. SROI will be computed as the ratio of “benefits” to “total investment” for each participant and is expressed as percentage. Participants’ earnings in both competitive and non-competitive jobs, education, and apprenticeship hereby account as “benefits.” “Investments” are defined at the total vocational program costs per patient and total costs of mental health service [22, 50–52].

For the intervention group specifically, we included two instruments analyzing *efficacy belief and work alliance*: the Job Search Self-Efficacy scale (JSSE-O), which bases on the tripartite efficacy beliefs model and examines components of self-efficacy, and other efficacies and relation-inferred self-efficacy [53]. The scale consists of 10 items measuring participants’ belief about the success of the job search. Additionally, we included the WAI-VR [54], a modified version of the Working Alliance Inventory (WAI; [55]). It consists of 12 items that examine the factors bond, task and goal.

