#### Secondary outcomes

As a sensitivity analysis to the primary efficacy, a logistic regression model will be applied with additional covariates age and gender. Descriptive methods will be used for the analyses of the other secondary outcomes, including calculation of appropriate summary measures of the empirical distribution as well as 95% confidence intervals and calculation of descriptive two-sided p-values.

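### SROI is fixed as a ratio per participant, and no usual summary of such ratios gives the return on the money invested; with widely dispersed costs the arm order can even reverse

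*Protocol article*

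**What the plan says.** The economic outcome is described under Plans for assessment and collection of outcomes {18a}. SROI is meant to capture the "value of social benefits created by a program in relation to the relative cost of achieving those benefits". It is the ratio of benefits to total investment at 12 months, computed "for each participant and is expressed as percentage". The numerator is what a participant earns, whether in competitive or other jobs, in education or in an apprenticeship. The denominator is "defined at the total vocational program costs per patient and total costs of mental health service".

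The abstract lists SROI among the secondary employment outcomes. The Secondary outcomes part of the statistical methods analyses the other secondary outcomes descriptively, including "calculation of appropriate summary measures of the empirical distribution as well as 95% confidence intervals and calculation of descriptive two-sided p-values". It does not say whether the mean, the median or another summary is used for SROI. Nowhere does the article compute SROI from arm totals or arm means, or as extra benefit against extra cost.

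**The concern.** The stated purpose concerns a programme: what it yields in relation to what it costs. That is total benefits over total costs. The stated computation concerns a person, and the statistical section then describes the distribution of those personal ratios. The two are different quantities.

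A participant with few service contacts and some wages gets a very large ratio, while an expensive participant without wages gets zero. An average of such values can be driven by a few low-cost earners. The distortion may also differ between arms. Every SEE participant is assigned a SEE-specialist, which puts a minimum under the SEE denominators. TAU participants may have less vocational cost, so very small denominators may be commoner there.

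The background and the discussion both name the economic evaluation as an advance over earlier trials. The reported figure should therefore answer the question the article sets for it.

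**Working it through.** The article states no SROI figure, cost or earnings distribution, so there is nothing to reproduce. All euro values, earner shares, CVs and correlations below are assumptions.

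**1. What each summary measures.** Let B be a participant's benefits and C the investment.
- Return on the money invested: ΣB / ΣC. This equals Σ C·(B/C) / ΣC, a cost-weighted average of the individual ratios.
- Mean of individual ratios: (1/n) Σ B·(1/C). Each participant's earnings are weighted by 1/C.
- Median of individual ratios: zero whenever fewer than half the arm has earnings. The planning rates for the primary outcome are 40% and 16%. If the share with any earnings were near these, both medians would be zero.

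**2. Two participants per arm.**

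| Arm | Earnings (EUR) | Costs (EUR) | Individual ratios | Mean of ratios | Ratio of totals |
|---|---|---|---|---|---|
| TAU | 6,000; 2,000 | 1,000; 19,000 | 600%; 10.5% | 305% | 8,000/20,000 = 40% |
| SEE | 8,000; 8,000 | 8,000; 12,000 | 100%; 66.7% | 83% | 16,000/20,000 = 80% |

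Both arms spend the same and SEE earns twice as much, yet the mean of ratios favours TAU.

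**3. A larger illustration.** Assume lognormal service costs with mean EUR 8,000, earners 20% TAU vs 40% SEE with mean earnings of EUR 8,000, a SEE programme cost of EUR 4,000, and no vocational cost in TAU.
- Return on total spending, TAU: 0.20 × 8,000 / 8,000 = 20%.
- Return on total spending, SEE: 0.40 × 8,000 / (8,000 + 4,000) = 3,200/12,000 = 27%.
- Mean of ratios in TAU when cost and work are independent: for a lognormal cost, E(1/C) = (1 + CV²)/mean, so the mean ratio is 0.20 × (1 + CV²). This gives 25%, 40% and 65% at CV 0.5, 1.0 and 1.5.
- The SEE values, and all values with correlation, are E(B/C) evaluated numerically. The correlation is between log cost and a latent normal variable that determines who earns.

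| Cost CV | Correlation of cost and work | Mean of ratios, TAU | Mean of ratios, SEE | Order |
|---|---|---|---|---|
| 0.5 | 0 | 25% | 29% | kept |
| 0.5 | −0.3 | 30% | 32% | kept |
| 0.5 | −0.5 | 34% | 33% | near tie |
| 1.0 | 0 | 40% | 34% | reversed |
| 1.0 | −0.5 | 67% | 41% | reversed |
| 1.5 | 0 | 65% | 38% | reversed |
| 1.5 | −0.5 | 124% | 47% | reversed |

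**4. Sensitivity to the assumptions.**
- Add EUR 1,500 of vocational cost to each TAU participant: no reversal in any of 12 settings (CV 0.5, 0.75, 1.0, 1.5; correlation 0, −0.3, −0.5). At CV 1.0 and correlation 0 the means are 25% TAU vs 34% SEE. At CV 1.5 and correlation −0.5 they are nearly tied.
- Add only a minimum care cost of EUR 2,000: 31% vs 32% at CV 1.0 and correlation 0, so that reversal disappears. Reversals remain at higher CV or stronger correlation.
- Use 16% vs 40% as earner shares with no TAU vocational cost: 32% vs 34% at CV 1.0 and correlation 0, no reversal.
- Use other values (mean cost EUR 10,000, 16% vs 40% earners, SEE cost EUR 2,000 or 5,000, CV 0.5 to 2, correlation 0 to −0.6): reversal in 13 of 24 settings, none of them at CV 0.5. The ratio of totals favoured SEE in all 24.

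**The case against.** The strongest reply is that the article never says the ratios will be averaged. It speaks of appropriate summary measures, and the choice of summary for a skewed secondary outcome can be left to a statistical analysis plan that is not shown. This stands as far as the mean goes. It does not remove the point, because the per-participant ratio is already fixed in the article. Changing from mean to median only exchanges one unsuitable summary for another that may be zero in both arms.

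A second reply concerns the arm asymmetry. Under Explanation for the choice of comparators {6b}, TAU includes referral to external government-funded vocational programmes, social work counselling and at least one consultation on work or education. The definition of investments does not limit vocational costs to SEE. TAU denominators may therefore be less small than the illustration supposes, and step 4 shows that this alone can remove the reversal. That part stands in full.

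A reader might infer that the planned SROI will make SEE look the worse investment, or that reversal is the usual result. The documents do not support this: they give no cost or earnings data, and several plausible settings keep the order. A reader might also infer that counting non-competitive earnings, or giving unpaid education no monetary value, is an error. These are explicit choices in the definition. SROI need not mirror the primary outcome, and educational attainment is a separate secondary outcome.

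Finally, SROI is secondary and descriptive, and monthly wages are reported separately. This limits the consequence.

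**Conclusion.** The point holds in a limited form. The computation fixed in the article does not match the purpose it states: neither the mean nor the median of individual ratios gives the return on total spending. This follows from the algebra and needs no assumed values.

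The size does need them. In the illustration with no TAU vocational cost, a return on spending of 20% vs 27% appears as anything from 25% vs 29% to 124% vs 47%. The arm order can reverse when costs are widely dispersed (CV of about 1 or more in most of the settings tried) and TAU carries little vocational cost. It need not reverse, and whether it would in this trial cannot be judged from the article. The primary conclusion is unaffected. The change is worth making because the economic evaluation is one of the trial's named advances and the remedy is cheap.

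**What to change.** Define SROI for each arm as total (or mean) benefits divided by total (or mean) investments. Give a bootstrap 95% CI, resampling participants within arm, for each arm and for the between-arm contrast.

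Add the incremental comparison: difference in mean benefits minus difference in mean costs, with a CI. It answers a separate question. In the illustration the benefit difference is 3,200 − 1,600 = EUR 1,600 and the cost difference is EUR 4,000, so the net is −EUR 2,400 over 12 months even though SEE has the higher average return. Readers need both results.

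Keep the per-participant ratios as descriptive information only. The definition of which earnings count as benefits can stay as it is.

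The cost is a few lines of definition and a little more analysis work on the same data. The downside is that individual SROI values are no longer the main economic result.

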**Methods:**

The SEEearly trial compares treatment as usual (TAU) plus SEE to TAU alone in outpatient psychiatric settings. The study is a six-site, two-arm, single-blinded, superiority randomized controlled trial (RCT). Participants are randomly assigned (1:1) to the intervention or control group. Aiming to recruit 184 participants, with an assumed drop-out rate of 22%, we will be able to detect a 24% difference in the main outcome of employment/education with 90% power. We make assessments at baseline and at 6- and 12-month follow-ups. Outcome data on employment/education, medication, and current psychiatric treatment is obtained monthly through phone based short assessments. The primary outcome is steady participation for at least 50% of the 12-month follow-up in competitive employment and/or mainstream education. Secondary employment outcomes capture length of employment/education, time to first employment/education, monthly wages/educational attainment, and social return on investment (SROI). Secondary non-employment outcomes include subjective quality of life, psychopathology, substance use, relapse, hospitalization, and functional impairment. To be eligible, participants must be between 16 and 35 years, fulfill diagnostic criteria for early psychosis, and be interested in competitive employment and/or mainstream education.

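### SROI is defined as one ratio per participant, and summarising those ratios does not in general give the programme-level return that the protocol describes

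*Protocol article*

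**What the plan says.** The economic paragraph of the protocol article, under Plans for assessment and collection of outcomes {18a}, does three things.

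- It gives the purpose: SROI is "designed to survey the value of social benefits created by a program in relation to the relative cost of achieving those benefits".
- It fixes the unit: benefits over total investment "for each participant and is expressed as percentage".
- It names the parts. Participants' "earnings in both competitive and non-competitive jobs, education, and apprenticeship hereby account as" benefits, and investments are "defined at the total vocational program costs per patient and total costs of mental health service".

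The abstract lists SROI among the secondary employment outcomes, and Table 1 places it at month 12. Under Statistical methods {20a}, Secondary outcomes, the outcomes other than the primary are analysed descriptively, "including calculation of appropriate summary measures of the empirical distribution as well as 95% confidence intervals" and descriptive two-sided p-values. No arm-level ratio of total benefits to total investment is mentioned.

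**The concern.** The stated purpose concerns a programme: what was gained for what was spent. That is total benefits divided by total investment. The stated computation forms a ratio for each person, and the analysis section then summarises the distribution of such values. A mean of those ratios weights every participant equally, whatever was spent on them, so an earner with low cost can dominate it.

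The arms are not affected alike. The comparison is TAU plus SEE against TAU, so the SEE arm carries an added programme cost. That cost makes its denominators relatively less variable. A comparison of mean ratios can therefore move for reasons unrelated to return per euro. The Background and the Discussion both present the economic evaluation as an advance over earlier trials, so its main figure should measure what it is said to measure.

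**Working it through.** **Inputs from the documents.** The ratio is per participant, benefits are earnings, investment is vocational programme cost plus mental health service cost, and SEE is added to TAU. No cost, earnings figure or target SROI is stated, so there is no SROI figure to reproduce. All amounts below are assumptions.

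**1. Exact gap.** Let B be benefit, C cost and R = B/C. Then mean(B) = mean(R × C) = mean(R) × mean(C) + Cov(R, C). Hence

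mean(R) - sum(B)/sum(C) = -Cov(R, C)/mean(C).

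The gap is zero only if ratio and cost are uncorrelated, and it can take either sign.

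**2. Two-person check.** Earnings are 6,000 and 0; costs are 2,000 and 18,000.
- Mean of ratios: (3 + 0)/2 = 150%.
- Return on money spent: 6,000/20,000 = 30%.
- Cov = 3,000 - 1.5 × 10,000 = -12,000, so the gap is 12,000/10,000 = 1.2, or 120 points, as it should be.

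**3. Earnings independent of cost.** The overstatement factor is E[1/C] × E[C]. For log-normal TAU cost it equals 1 + CV². For SEE, a fixed cost f (in units of mean TAU cost) is added to C, giving E[1/(C + f)] × (1 + f), evaluated numerically.

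| Cost CV | TAU | SEE, f = 0.25 | SEE, f = 0.5 | SEE, f = 1.0 |
|---|---|---|---|---|
| 0.5 | 1.25 | 1.14 | 1.10 | 1.05 |
| 1.0 | 2.00 | 1.44 | 1.28 | 1.15 |

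**4. Earnings related to cost.** Take 40% earners in SEE and 16% in TAU, a fixed amount earned, f = 0.5, and a positive correlation between log cost and the latent propensity to earn.

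| Cost CV | Correlation | TAU | SEE |
|---|---|---|---|
| 0.5 | 0.3 | 1.00 | 1.01 |
| 0.5 | 0.5 | 0.85 | 0.94 |
| 1.0 | 0.5 | 0.99 | 1.02 |

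The 40% and 16% are borrowed from the sample-size section. There they are steady-participation rates, not shares with earnings, so their use here is also an assumption.

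**5. Effect on the arm comparison.** Assume earnings of 9,000 if any, mean service cost 10,000, SEE cost 5,000, and no vocational programme cost in TAU. The ratio of totals is 0.40 × 9,000/15,000 = 24.0% for SEE and 0.16 × 9,000/10,000 = 14.4% for TAU, a difference of 9.6 points. The mean of ratios gives:
- CV 0.5, independent: 26.3% against 18.0%, difference 8.3.
- CV 1.0, independent: 30.6% against 28.8%, difference 1.8.
- CV 0.5, correlation 0.5: 24.0 × 0.945 = 22.7% against 14.4 × 0.853 = 12.3%, difference 10.4.

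**6. Median.** If more than half of an arm has no earnings, the middle ratio is zero whatever the others earn. In the example the median is 0% in both arms.

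**The case against.** The best defence is that the plan fixes a participant-level variable and not the arm-level statistic. The secondary-outcomes section does not name SROI, a mean or a median; it speaks of appropriate summary measures. A ratio of totals uses the same data and is not excluded, and a health-economic plan may specify it. The per-participant form may also follow the earlier work that the protocol cites for it. This stands in part: that the arm result will be a mean is an inference. However, the text does commit to a ratio per person and to summaries of the distribution, and neither the mean nor the median of those ratios in general estimates the return described in the same paragraph.

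Three stronger readings are tempting, and the documents do not support them.

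- **The mean ratio always overstates the return.** The sign follows the covariance. A positive cost-earnings relation is plausible, because earnings from non-competitive jobs count as benefits, vocational programme costs count as investment, and TAU includes referral to external vocational programmes.
- **Control denominators are close to zero.** All participants receive TAU throughout, including medical review, pharmacological treatment, psychosocial support and at least one consultation on work or education. No cost figures are given.
- **The plan will rank TAU above SEE when SEE returns more.** Assume true returns of 40% and 50%, 92 per arm, f = 0.5 and independent costs. At CV 1.0, simulation ranks TAU first in about 64–71% of trials by mean of ratios, against 19–24% by ratio of totals. At CV 0.5 (f from 0.25 to 1.0) it is about 30–43% against 18–25%, so reversal is not the usual result. The example in step 5 keeps SEE ahead at CV 1.0 under independence.

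**Conclusion.** The point holds as a mismatch between a stated computation and its stated purpose. Summaries of individual ratios do not in general estimate the programme's return, and the discrepancy can differ between arms because only one carries the SEE cost.

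Its size cannot be known from the documents. Under independent log-normal costs and a fixed SEE cost of half the mean TAU cost, the overstatement is 1.25 (TAU) against about 1.1 (SEE) at cost CV 0.5, and 2.0 against about 1.3 at CV 1.0. It disappears if costs hardly vary, and it can vanish or reverse under positive cost-earnings correlation. External vocational costs in TAU could narrow the difference between arms. The statement on the median is conditional: the documents do not give the share without earnings.

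SROI is a secondary outcome with descriptive p-values. The primary analysis, the sample size and the confirmatory claim are untouched, so this is a worthwhile correction and no threat to the trial.

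**What to change.** State in the protocol or analysis plan that arm-level SROI is the sum of benefits divided by the sum of investments, in percent. Give a 95% confidence interval for each arm and for the between-arm difference by bootstrapping participants within arm (and site). Report the individual ratios, if wanted for comparability with earlier work, as description only and labelled as such.

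The cost is one sentence and a small amount of extra analysis. The participant-level benefits and costs are already needed for the individual ratios, so no new data are required.
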